## Methods/Design

The INITIATION study incorporates a model of care with the PN and primary care physician working as a team to initiate and titrate basal and prandial insulin in the Australian primary care setting. The new model of care is evaluated using a before and after study design. Resources have been developed to guide these primary care teams to effectively implement the study protocol (Figure 1). Support and mentorship will be provided to primary care physicians and PNs by the study CDE-RN and the study endocrinologist. Nested within this study is an exploratory trial of two different types of blood glucose monitoring. Participating T2D patients will be randomized to one of two arms, namely the self-monitoring of blood glucose (SMBG) alone (Freestyle Optium™; Abbott) or with an adjunct r-CGM (*i*Pro™2/Enlite™; Medtronic). Each patient will be followed for 24 weeks post-randomization with outcomes related to measures of glycemia (identification of elevated post-prandial glucose levels and the time required to reach target glycemia), quality of life and utilization of health professionals’ time spent with patients.

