**

HbA1c will be collected at baseline, 12 weeks and 24 weeks and analyzed by a DCCT aligned centralized laboratory.

#### **
*Follow-up and endpoint determination procedures*
**

The primary endpoint is the absolute change in HbA1c following insulin initiation at baseline compared with 24 weeks. The secondary endpoints include changes r-CGM time spent in low (<4.0 mmol/L), target (4.0-10.0 mmol/L) and high (>10.0 mmol/L) glucose range at baseline, 12 and 24 weeks; symptomatic hypoglycemia; incidence of severe hypoglycemia (hypoglycemia resulting in loss of consciousness or requiring third party assistance); proportion of patients being prescribed a prandial insulin (glulisine) injection; time to reach target HbA1c ≤7%; proportion of patients achieving an HbA1c ≤7% at 12 and 24 weeks); total insulin dose at 12 weeks and 24 weeks; change in quality of life (ADDQOL and SF-36v2 at 12 weeks and 24 weeks compared with baseline); blood pressure (12 weeks and 24 weeks compared with baseline) and weight change (BMI and waist-to-hip ratio at 12 weeks and 24 weeks compared with baseline).

Endpoints for the sub-study comparing r-CGM with SMBG reflect those described above. In addition, patients and PNs’ acceptability and utility of CGM devices at 24 weeks and total primary health care utilization at 24 weeks will be examined.

#### **
*Benchmark data*
**

The glycemic outcomes reflected by changes in HbA1c following implementation of this new model of care in primary care setting will be benchmarked against observational data collected from all patients with T2D commenced on insulin by private endocrinologists/CDE-RN teams over the same period. Data to be collected from benchmark patients at baseline, 12 weeks and 24 weeks include age, duration of diabetes, the presence of diabetic complications (laser requiring retinopathy, ischemic heart disease, lower limb ulceration or amputation, stroke), the frequency of home blood glucose monitoring, the need for an interpreter, employment status, whether they live alone, hospitalization within the last 12 weeks, current medications and HbA1c. These characteristics will allow a comparison of the demographic, costs and outcomes of those patients with T2D commencing insulin in the specialist centers with those in primary care.

#### **
*Sample size calculation*
**

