The power calculation was based on one sample comparison of mean against a reference value. The HbA1c reference value was 8.23% as reported in the INSTIGATE study [4] assuming no change in HbA1c without the intervention. The new model of care was estimated to result in HbA1c reduction of 0.4%. Based on a standard deviation of 1.44 in the FIELD study [30] with a two-sided alpha of 0.05 and 80% power, a sample size of 102 patients is required to detect change in the primary outcome. Our previous research suggests that in an average two full-time-equivalent primary care physician practice we expect to identify 80–100 patients with T2D. Of these we anticipate 10% (8–10) will meet our inclusion criteria and 50% recruitment rate, generating on average 4–5 participating patients per practice. A total of 22 primary care practices will be required. Our sample is not powered to detect change between SMBG and r-CGM but rather to explore the feasibility and efficacy of r-CGM in primary care.

#### **
*Statistical analysis*
**

The primary analysis will be the change in HbA1c based on the entire sample at baseline, 12 and 24 weeks. This analysis will produce a conservative estimate of the benefit of insulin therapy as glycemic control tends to rise without the introduction of insulin in this population. The changes in HbA1c will be benchmarked against those obtained from patients under specialist care who have been initiated on insulin. A secondary analysis will examine the absolute change in HbA1c between the r-CGM and SMBG groups. Comparisons of the entire sample as well as between r-CGM and SMBG will be made at baseline, 12 and 24 weeks for all secondary endpoints.

#### **
*Trial monitoring*
**

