A safety monitoring committee consisting of study endocrinologist, primary care physician and CDE-RNs will be appointed. All significant adverse events (which include hospital presentations or admissions) and their duration will be documented. All serious adverse events will be reported to the safety monitoring committee within 24 hours of the primary care team being made aware of them. Each adverse event will be independently reviewed by other chief investigators (consisting of 4 endocrinologists) independent of the safety monitoring team. Additionally, the Human Research Ethics Committee will be notified of all significant adverse events in writing. Criteria for withdrawal of study participants include major protocol violation, major adverse event directly related to the intervention, pregnancy, voluntary withdrawal of consent or development of life-threatening illness.

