To maximize acceptance in a busy and varied clinical environment, the tools designed to implement the intervention are flexible with a facility to be tailored to each practice’s structure and the individual needs of patients. The insulin initiation and titration protocol employs a simple unambiguous easy-to-follow algorithm guiding primary care physicians and PNs in a busy general practice setting. A basal insulin analogue is employed as it would minimize the risk of hypoglycemia. This precaution is crucial in order to ensure that the physician’s, PN’s and patient’s trust in the ability of the model of care to deliver a positive outcome is maintained. Insulin glargine is chosen because it is the only available basal insulin that is subsidized by the Pharmaceutical Benefits Scheme (PBS) for the management of T2D in Australia at the time this study is conducted. A basal plus approach, incorporating the rapid acting analogue, insulin glulisine, acknowledges the importance of addressing post-prandial hyperglycemia in reducing HbA1c in this patient group [32,33]. A similar disposable injecting device (Solostar™, Sanofi) mechanism used for both glargine and glulisine minimizes need for further education of primary care physicians, PNs and patients.

The insulin titration schedule is conservative, balancing sophistication against practicability. Its aim is to minimize hypoglycemia risk, and has been developed based upon the review of available research evidence [14] and clinical experience. Each physician-PN team will be able to deviate from the insulin initiation and titration protocol at their discretion. This should minimize patient adverse events and ensure that it is feasible for both PNs and physicians to implement this model of care within their current workload in real-world practice. Our aim is to embed and integrate the task of initiating and titrating insulin within the complex ongoing generalist work of primary care with minimal disruption to work in general.

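### The withdrawal rule removes participants, not only study procedures, for protocol violation or intervention-related harm, so some may lack the 24-week HbA1c that the entire-sample analysis needs

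*Protocol article*

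**What the plan says.** The sentence on withdrawal closes the Trial monitoring section: "Criteria for withdrawal of study participants include major protocol violation, major adverse event directly related to the intervention". The same list goes on to "pregnancy, voluntary withdrawal of consent or development of life-threatening illness". Major protocol violation is not defined.

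The endpoint and analysis sections assume full follow-up. Follow-up and endpoint determination procedures: "The primary endpoint is the absolute change in HbA1c following insulin initiation at baseline compared with 24 weeks". Statistical analysis: "The primary analysis will be the change in HbA1c based on the entire sample at baseline, 12 and 24 weeks". The opening of Methods/Design adds: "Each patient will be followed for 24 weeks post-randomization".

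On departures from the insulin protocol, the Discussion says: "Each physician-PN team will be able to deviate from the insulin initiation and titration protocol at their discretion". Intervention with participating patients gives the teams the same freedom.

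Nowhere does the article say that a withdrawn patient still has the 12- and 24-week HbA1c taken. Nor does it say that data already collected are discarded.

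**The concern.** Two of the listed criteria are events after enrolment that can arise from the model of care itself: failing to follow the protocol, and being harmed by the intervention. The study's primary aim covers feasibility as well as glycaemic outcome, so these patients carry information about the result. If they leave before week 24, the before-after change is estimated in a group selected by how the model performed in them.

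This has to be settled in the protocol. A statistical analysis plan can say how to treat missing values, but it cannot recover a blood test that was never taken.

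The nested comparison of r-CGM with SMBG is exposed too. Allocation is open to researchers, practices and patients, so a violation is judged with the arm known. The arms also differ in what can be violated. The r-CGM arm has weekly traces for four weeks, then fortnightly, then monthly. The SMBG arm has traces at baseline, 12 and 24 weeks, with an instruction not to titrate from them. Withdrawal could therefore differ by arm, although nothing shows that it will.

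Finally, the violation criterion is hard to apply consistently. Teams may depart from the insulin protocol at their discretion, and nothing marks where an allowed departure ends and a violation that ends participation begins.

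**Working it through.** **1. The planned sample size.** Sample size calculation says: "The power calculation was based on one sample comparison of mean against a reference value". The inputs given there are a reduction of 0.4 HbA1c points, SD 1.44, two-sided alpha 0.05 and power 80%.

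n = (SD × (z₀.₉₇₅ + z₀.₈₀) / δ)² = (1.44 × 2.8016 / 0.4)² = 101.72, rounded up to 102.

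The stated figure reproduces exactly (a t-based version gives 104). So 102 is the number needed with a 24-week value, and nothing is added for loss. The recruitment estimate offers little reserve: 22 practices at 4-5 patients each is 88-110.

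**2. Power if some patients have no 24-week HbA1c.** The article gives no withdrawal rate, so the rates below are assumptions. Power = Φ(0.4/1.44 × √n − 1.96), with n rounded down; enrolment to keep 102 evaluable = 102/(1 − loss), rounded up.

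| Assumed loss | n with 24-week value | Power | Enrolment needed to keep 102 |
|---|---|---|---|
| 5% | 96 | 77.7% | 108 |
| 10% | 91 | 75.5% | 114 |
| 15% | 86 | 73.1% | 120 |
| 20% | 81 | 70.5% | 128 |

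For 10%: 0.2778 × √91 = 2.650; 2.650 − 1.960 = 0.690; Φ(0.690) = 0.755.

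**3. Bias in the mean change.** Let w be the fraction withdrawn, C the mean change in completers, and D the mean change in withdrawn patients minus C (positive means worse). The all-patient mean is (1 − w)C + w(C + D) = C + wD, so an analysis of completers alone is off by wD.

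- Assumed w = 5%, D = 0.5: 0.05 × 0.5 = 0.025 points, 6% of 0.4.
- Assumed w = 15%, D = 1.0: 0.15 × 1.0 = 0.15 points, 38% of 0.4.
- D = 0: no bias at any w.
- D negative: the error reverses. With w = 10% and D = −0.5, benefit is understated by 0.05.

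**4. The same check anchored on the planned effect.** Suppose the true all-patient change is −0.40 and 10% are withdrawn. Then C = (−0.40 − 0.10 × withdrawn change)/0.90.

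- Withdrawn patients change by −0.40: completers show −0.40.
- Withdrawn patients do not change: completers show −0.44.
- Withdrawn patients worsen by 0.4: completers show −0.49.

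At 20% the last two become −0.50 and −0.60.

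**The case against.** A reader might infer that the plan strips poor outcomes out of the primary analysis. The text does not say that. It lists reasons for withdrawal and is silent on whether HbA1c collection stops. Read with the statements that each patient is followed for 24 weeks and that the entire sample is analysed, it could even mean that withdrawn patients are still measured. A journal article also condenses, and the handling of withdrawn patients and the definition of a major violation may sit in the full protocol.

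A reader might also infer bias towards benefit. That is not established. A patient withdrawn for severe hypoglycaemia need not have a high HbA1c, and a protocol violator need not have done badly. The rates and differences used above are assumptions, and small ones give small answers: 2% withdrawn with a 0.5-point difference is 0.01 points.

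Nor would harms go unrecorded. Severe and symptomatic hypoglycaemia are secondary endpoints, and significant adverse events are documented and independently reviewed. The comparison of monitoring arms is declared exploratory and unpowered. The freedom to deviate may also narrow what counts as a violation, so few patients might be affected.

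All of this limits the point, but part of it remains. The rule as printed withdraws participants, two of its criteria are tied to how the intervention performs, and the general follow-up statement does not say which text prevails once a patient meets one of them. That is a conflict between stated passages, not a detail left for later.

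**Conclusion.** The point holds as a conflict between a stated withdrawal rule and the stated analysis population. As written, patients who meet the violation or intervention-related adverse-event criterion may have no 24-week HbA1c, and the entire-sample analysis could become one of patients who tolerated and followed the model.

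The direction and size of any bias cannot be determined from the article. The range of about 0.03-0.15 points rests wholly on the assumed 5-15% withdrawn and 0.5-1.0 points worse change. The effect on power needs no assumption about direction, only about the rate of loss.

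The article calls its estimate conservative because glycaemic control tends to worsen without insulin. That argument does not cover selective loss. The change is worth making because it is cheap and has to be in place before patients are lost.

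**What to change.** Separate stopping study procedures from leaving follow-up:

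- State that a patient who meets the protocol-violation or intervention-related adverse-event criterion may stop study procedures but stays in follow-up. The scheduled 12- and 24-week HbA1c is collected and included in the entire-sample and by-arm analyses, unless the patient withdraws consent for data collection.
- Drop major protocol violation as a reason to end follow-up, and report such cases by arm as a feasibility result.
- Reconcile the term with the deviations allowed in Intervention with participating patients and in the Discussion.

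Clinical decisions on stopping treatment, and the handling of pregnancy and life-threatening illness, stay as they are.

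The cost is a change of wording and at most two blood tests per affected patient, both already scheduled. The observed effect may turn out smaller once these patients are counted.

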## Discussion

Delays in the timely initiation of insulin are often attributed to “psychological insulin resistance” [31] on the part of patients and “clinical inertia” on the part of health professionals. However, barriers associated with the health system responsible for the provision of medical services are also important. The model of care under evaluation in this study attempts to address barriers which may be responsible for delaying insulin initiation in primary care while also utilizing those strengths inherent in the primary care model. Our previous work [21] has identified that the organization within the practice, clarification of the roles and expectations of patient and health professionals involved in insulin initiation and delegation of responsibility for the provision of care are key factors in determining success. Our study introduces a new model of care in Australia, with an enhanced role for the PNs working in partnership with the primary care physicians, supported by CDE-RNs and endocrinologists. This model addresses the barriers and enablers of insulin initiation in the primary care setting at the practice, health professional and patient level. It also utilizes the current healthcare system and financial structures in Australia ensuring immediate generalizability.

To maximize acceptance in a busy and varied clinical environment, the tools designed to implement the intervention are flexible with a facility to be tailored to each practice’s structure and the individual needs of patients. The insulin initiation and titration protocol employs a simple unambiguous easy-to-follow algorithm guiding primary care physicians and PNs in a busy general practice setting. A basal insulin analogue is employed as it would minimize the risk of hypoglycemia. This precaution is crucial in order to ensure that the physician’s, PN’s and patient’s trust in the ability of the model of care to deliver a positive outcome is maintained. Insulin glargine is chosen because it is the only available basal insulin that is subsidized by the Pharmaceutical Benefits Scheme (PBS) for the management of T2D in Australia at the time this study is conducted. A basal plus approach, incorporating the rapid acting analogue, insulin glulisine, acknowledges the importance of addressing post-prandial hyperglycemia in reducing HbA1c in this patient group [32,33]. A similar disposable injecting device (Solostar™, Sanofi) mechanism used for both glargine and glulisine minimizes need for further education of primary care physicians, PNs and patients.

The insulin titration schedule is conservative, balancing sophistication against practicability. Its aim is to minimize hypoglycemia risk, and has been developed based upon the review of available research evidence [14] and clinical experience. Each physician-PN team will be able to deviate from the insulin initiation and titration protocol at their discretion. This should minimize patient adverse events and ensure that it is feasible for both PNs and physicians to implement this model of care within their current workload in real-world practice. Our aim is to embed and integrate the task of initiating and titrating insulin within the complex ongoing generalist work of primary care with minimal disruption to work in general.

### The use of blood glucose monitoring among T2D in primary care

Once insulin has been initiated, the ongoing monitoring and review of glucose levels by the patient and health professional is important for patient safety and for intensification of insulin therapy [13] as this provides insight into recurring patterns of glycemia, the impact of diet and behavior upon glycemia and the effect of therapeutic interventions [34]. However hypoglycemia may be undetected particularly when it occurs overnight [35] and identifying post-prandial glycemia may be a challenge for clinicians.

The use of r-CGM offers the potential for identification of unrecognized hypoglycemia and hyperglycemia excursions [36] leading to more tailored and appropriate treatment changes. We chose the *i*Pro™2 r-CGM device as it is small, convenient and non-intrusive for the patient to wear and is essentially “wear and forget”. It requires a minimum of two blood glucose meter readings each day for calibration. The study protocol will result in the first widespread use of these devices in a “real world” primary care setting where people with T2D receive the majority of their health care. Given the exploratory nature of the r-CGM arm of the study the design incorporated an intensive r-CGM regimen providing a level of redundancy sufficient to allow for potential device failures.

### Study design issues

We have undertaken a series of studies of insulin initiation in primary care based on the UK Medical Research Council (MRC) complex intervention framework [37]. In the pre-clinical phase, we examined barriers and enablers of insulin initiation using qualitative approach [21] drawing upon the Normalization Process Theory [38]. We then developed and piloted our new model of care on insulin initiation in five general practices in Melbourne, Australia as part of Phase 1 modeling stage of the MRC framework [39]. Our new model of care is complex as it is made of several interconnecting factors [40] and it is embedded within the ‘real world’ general practice setting. In the INITIATION study, we will progress to a Phase 2 exploratory trial to further refine our intervention and processes as well as to determine the feasibility of our study protocol in a much larger sample of 22 general practices. The exploratory trial stage is considered important to inform a future definitive randomized controlled trial.

Our study is based in primary care involving “research naive” practices. Data collection forms and titration algorithms need to be easily understood and not time consuming to complete and follow as the practices will receive limited reimbursement for their participation in research. The primary aim of implementing the new model of care is not only to achieve insulin initiation but also the treatment intensification required to achieve appropriate glycemic control in a safe manner. The number of people who transition to prandial insulin and timeliness with which that occurs is therefore also of importance and this is reflected in the study’s secondary endpoints. Other secondary endpoints include indicators clinically relevant to health professionals and patients when commencing insulin, including quality of life and weight gain.

Our primary care practices will be a convenience sample of practices in the state of Victoria and thus will not be representative of all Australian primary care practices. A convenience sample is within the scope of this before and after study with a nested exploratory trial to examine the impact of our new model of care and observe the feasibility of r-CGM use among T2D in primary care. Data relating to insulin initiation from a specialist setting in the same locality as that from which the practices will be recruited will be used to benchmark study outcomes. This is incorporated into the study design as assigning patients with suboptimal glycemic control judged by their primary care physicians as requiring insulin on clinical grounds to a control “no insulin” group is not ethically justifiable. Insulin initiation and titration in the specialist setting is accepted as the “gold standard” care and the benchmarking data will enable us to compare how our new primary care based model of care performed in improving HbA1c at 12 and 24 weeks. The benchmarking data will be the basis for a health economics analysis comparing the costs of insulin initiation in the primary care setting versus that in the specialists setting. A centralised laboratory for HbA1c testing will be used in this study to ensure that our study HbA1c result is consistent across participating primary care practices.

Cluster randomization of monitoring arms according to the primary care centres recruited for the study would have been appropriate had we planned a definitive effectiveness trial powered to identify difference in the change in HbA1c. Given that the study is not powered to do so, our individually randomized exploratory design will allow all practitioners to gain some experience and exposure to the use of r-CGM, thus maximizing our capacity to identify strengths and weaknesses in its use in the field.

